### Instruments

#### Quantitative data

We will collect baseline demographic information on all participants, including youth age, disability, mobility, health status, ethnic or cultural background, where the youth is living and with whom, and the size of their home community.

At baseline, and at three follow-up time points, all youth will complete measures of self-determination and self-efficacy using an online survey. The Arc’s Self-Determination Scale (SDS) adolescent version includes four subscales (autonomy, self-realization, empowerment, and self-regulation) and provides an overall score of self-determination [33]. Self-determination percentile scores can be generated based on norms from a population of US special education students (ages 14 to 22 y) with a wide range of disabilities. Internal consistency is high (Cronbach’s alpha = 0.90) and criterion-related validity is adequate (*r* = 0.25 to 0.5) [34]. The youth will complete all of the subscales except the self-regulation subscale, which uses a story-writing format requiring subjective scoring and can be sensitive to geographic, cultural, and socioeconomic differences among participants [33]. The General Self-efficacy Scale (GSE) is a 10-item self-administered tool with a 4-point Likert response scale [35] and has been used in numerous research studies to examine perceived self-efficacy. It is valid and reliable with internal consistencies ranging from 0.75 to 0.91.

In addition, a number of measures will be collected on-site during the RILS programs for Group A participants. Trained observers will complete the 48-item Measure of Environmental Qualities of Activity Settings (MEQAS-48) to capture program opportunities. Validated with life skills program activity settings, the MEQAS is a reliable and valid measure of aesthetic, physical, social, and opportunity-related qualities of leisure activity settings for youth with or without disabilities [36]. Observers use a 7-point scale to rate the extent to which the observed activity setting includes various features. The MEQAS has a sound factor structure and preliminary evidence of internal consistency, inter-rater reliability, and test-retest reliability. Cronbach’s alpha for the scales (Comfortable Place-related Qualities, Pleasant Physical Environment, Opportunities for Choice, Opportunities for Privacy/Relaxation, Opportunities to Interact with Peers, Opportunities for Personal Growth, Opportunities for Physical Activities, Opportunities for Cooperative Group Activity, and Opportunities to Interact with Adults) range from 0.82 to 0.97 [36]. Inter-rater reliability and test-retest reliability were established on a previous version, the MEQAS-32, with inter-rater reliability (ICC) ranging from 0.60 to 0.93 and test-retest reliability ranging from 0.70 to 0.90. The MEQAS-48 is available at https://flintbox.com/public/project/25723/

Trained observers will also complete the Service Providers’ Strategies-Checklist (SPS-C), a 24-item checklist that captures service providers’ actual use of intervention strategies in life skills programs, including teaching/learning techniques, handling/physical interventions, socially-mediated strategies, cognitive strategies, and non-intrusive strategies. Items were constructed based on service providers’ descriptions of their use of strategies in a qualitative study of RILS service providers and an existing checklist of intervention strategies for school-based therapy [37]. Content validity of the SPS-C was established through review by RILS service providers and clinicians on the research team, and it has a high inter-rater agreement (96 %). The SPS-C will allow us to characterise and compare the strategies used by service providers across the RILS programs. The SPS-C is available at http://flintbox.com/public/project/27313/

To capture in-the-moment experiences during the program, youth will complete the Self-Reported Experiences of Activity Settings (SEAS) measure [38] following selected program activities. The SEAS is a 22-item, youth-completed measure of situation-specific experiences, assessing Personal Growth, Psychological Engagement, Social Belonging, Meaningful Interactions, and Choice & Control. Internal consistency of the SEAS is good to excellent (Cronbach’s alpha from 0.71 to 0.88), with moderate test–retest reliability (mean scale intra-class correlation coefficient = 0.68) [38]. The SEAS is available at https://flintbox.com/public/project/25724/

The schedule of data collection for the study is shown below, in Table 1. All of the measures have been piloted in a RILS program [29]. This pilot work indicated that RILS program features and youth experiences can be reliably and meaningfully assessed *while they are occurring,* and the convergence between the measures demonstrated that youth experienced the program as service providers intended. The measures employed in this current study therefore have demonstrated high feasibility [29].

**Table 1 Tab1:** Schedule of research activities by group

Research Activities	Baseline	During Life Skills Programs	Follow-up		
			1 week post-program	3 months post-program	12 months post-program
Enrollment:					
Eligibility Screen	A, B, C, D				
Informed Consent	A, B, C, D				
Demographic Form	A, B, C, D				
Intervention:					
Life Skills Programming		A, C			
Life Skills Program Assessments:					
Service Providers’ Strategies-Checklist (SPS-C)		A			
Measure of Environmental Qualities of Activity Settings (MEQAS)		A			
Participant Assessments:					
Self-Reported Experiences of Activity Settings (SEAS)		A			
Arcs’s Self-Determination Scale	A, B, C, D		A, B, C, D	A, B, C, D	A, B, C, D
General Self-Efficacy Scale (GSE)	A, B, C, D		A, B, C, D	A, B, C, D	A, B, C, D
Qualitative Interview	A, C			A, C	A, C

**Group A**: Participants drawn from the youth enrolled in Residential Immersive Life Skills programs*.*
**Group B**: Participants drawn from the youth deferred from Residential Immersive Life Skills programs*.*
**Group C**: Participants drawn from youth enrolled in non-residential Life Skills programs*.*
**Group D**: Participants not participating in any group life skills program

#### Statistical power

We will recruit 30 youth in each of the four study groups in each of the 3 years of recruitment. This will result in a total of 90 youth participants per group. We have allowed for a liberal attrition rate of one-third, which will yield a minimum enrolment of 60 youth per group, sufficient for all analyses. A sample of 50 participants in each group will provide adequate power to detect moderate effect sizes (d = 0.50) on the primary outcome of self-determination, based on the following assumptions: power = 0.80, β = 0.20, α = 0.05 (one-tailed) [39]. Therefore, our projected sample of 60 youth will be sufficient to show any statistically significant changes in outcomes.

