### Data analysis

#### Quantitative analysis

Data from the online instruments (SDS and GSE) will be downloaded into an Excel spreadsheet. Data collection for the SPS-C, MEQAS, and SEAS will use hard copies of the instruments, with data entered into the Excel spreadsheet for data management. The Excel file will then be imported into SPSS for analysis. A portion of the data will be double entered to check for accuracy. The data from the two outcome measures (SDS and GSE) will be analysed descriptively to report means and standard deviations, pre, post, and at both follow-ups (3 and 12 months). The amount of change in the outcomes will be determined across the data collection time points. Baseline (pre-program) scores of all groups will be compared using t-tests to determine whether there are significant differences between groups on the dependent variables. Attrition rates for the groups will be calculated, to determine whether differential attrition is an issue. The RILS group (Group A) will be tested against one comparison group (Groups B, C or D) in each analysis. The primary analysis will therefore be a series of two between (study groups) and three within (longitudinal measurement points) repeated measures analyses of covariance (ANCOVAs), controlling for baseline scores, with the outcome measures as the dependent variables. Effect sizes will be calculated based on difference in pre- to post-test means, using Cohen’s D, with effect sizes between 0.30 and 0.50 considered medium and those >0.60 considered large [42]. We will use multilevel modeling to assess the proportion of variance in our outcome measures associated with the three program sites.

We will describe RILS program features by calculating means and standard deviations of the MEQAS scores and examining patterns of strategy use in the SPS-C data. The SEAS data for individual youth will be collapsed within each activity setting to provide an aggregate activity profile. We will examine convergence and correspondence between the SEAS and the SPS-C and/or MEQAS. Our previous pilot work demonstrated convergence between scores on the MEQAS (observable program features) and SPS-C (observable service provider strategies) [29]. Scores on the SEAS were also further enhanced by youth-reported experiences captured during brief interviews. These initial indicators of conceptual congruence will be further explored during this study.

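### The stated power fits one one-tailed two-group comparison, not the planned repeated-measures ANCOVAs, and the claim that 60 per group suffices for any change and every analysis is false

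*Protocol article*

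**What the plan says.** The Statistical power section of the protocol article plans 30 youth per group per year for three years: "This will result in a total of 90 youth participants per group". After one-third attrition it projects at least 60 per group and calls that number enough for every analysis. The benchmark behind this is "A sample of 50 participants in each group will provide adequate power", where the target is a moderate effect of d = 0.50 and the primary outcome is self-determination. The inputs are introduced with the words "based on the following assumptions: power = 0.80, β = 0.20, α = 0.05 (one-tailed"). The section ends by stating that "our projected sample of 60 youth will be sufficient to show any statistically significant changes in outcomes".

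The Quantitative analysis section sets Group A against one of Groups B, C or D in each analysis. It then says: "The primary analysis will therefore be a series of two between (study groups) and three within (longitudinal measurement points"). These are repeated-measures ANCOVAs controlling for baseline, with both outcome measures (SDS and GSE) as dependent variables. The section names no one-sided test. Its effect-size scale reads "with effect sizes between 0.30 and 0.50 considered medium". The Aims section describes the outcome question as change and/or maintenance, without a direction.

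**The concern.** The two sections describe different tests. The sample size rests on a directional comparison of two means at one time, for one outcome. The primary analysis is a set of ANCOVA F-tests for three comparators and two outcomes. An F-test rejects for differences in either direction unless a one-sided test of the 1-df group effect is laid down. The group-by-time test over three follow-ups has 2 df and cannot be made one-tailed.

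The one-tailed assumption also makes the stated power look better than the usual two-sided test would on the same model. The closing sentence then turns a calculation for one effect size on one outcome into an assurance about any change on any outcome. At stake is whether the protocol describes correctly what its sample can detect. This matters most for smaller contrasts. Group C also receives life skills programming (Table 1), so a smaller difference from Group A is plausible there, although the documents give no effect size for that contrast.

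**Working it through.** **Inputs.** From Statistical power: d = 0.50, power 0.80, α = 0.05 one-tailed, 50 per group as benchmark, 90 recruited and 60 projected per group. From Quantitative analysis: pairwise A versus B, C or D; three follow-ups; baseline as covariate; medium band 0.30 to 0.50. The documents give no correlation between time points, so every correlation below is an assumption.

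**Attrition.** 90 × (1 − 1/3) = 60. Consistent.

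**Formula, simple model.** For two groups of n, the noncentrality is d × √(n/2) with 2n − 2 df. Power is the probability that the noncentral t exceeds the critical value.

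**Step 1: reproduce the plan.** n = 50, d = 0.50: noncentrality 0.50 × √25 = 2.50, 98 df. The one-tailed critical value is 1.661, and power is 0.799. The plan's 80% is reproduced.

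**Step 2: same model, two-sided 0.05.**

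| n per group | d | Noncentrality | One-tailed power | Two-sided power |
|---|---|---|---|---|
| 50 | 0.50 | 2.50 | 0.799 | 0.697 |
| 60 | 0.50 | 2.74 | 0.859 | 0.775 |
| 64 | 0.50 | 2.83 | 0.879 | 0.802 |
| 90 | 0.50 | 3.35 | 0.955 | 0.916 |
| 60 | 0.30 | 1.64 | 0.496 | 0.371 |
| 60 | 0.20 | 1.10 | 0.289 | 0.192 |

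Two-sided 80% at d = 0.50 needs 64 per group (63 gives 0.795). With 60 per group the effect detectable with 80% power is d = 0.52 two-sided and d = 0.46 one-tailed.

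**Step 3: move towards the planned analysis.** With one follow-up adjusted for a baseline correlated r with it, the residual variance is 1 − r². For r = 0.5 it is 0.75, so the noncentrality is d × √(n/2)/√0.75. At n = 60, two-sided, this gives 0.88 for d = 0.50 and 0.47 for d = 0.30.

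The ANCOVA group effect averages three follow-ups. Assume compound symmetry with correlation r and a group difference that is constant over time. The variance is then (1 + 2r)/3 − r²:

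- r = 0.3: 1.6/3 − 0.09 = 0.443
- r = 0.6: 2.2/3 − 0.36 = 0.373

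At n = 60, two-sided, r from 0.3 to 0.6 gives 0.98 to 0.99 for d = 0.50 and 0.69 to 0.76 for d = 0.30. At n = 50 and d = 0.50 the range is 0.96 to 0.98.

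These last figures are for the group main effect only. They do not apply to the group-by-time test, for which the documents give too little to compute power.

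**The case against.** The strongest reply is that nothing is miscalculated. The inputs are stated openly and yield 50 per group. The design enrols 90 and expects at least 60, so the benchmark of 50 is not the planned size. At 60, the two-sided shortfall on the simple model is only about 2.5 points (0.80 − 0.775). The planned ANCOVA also uses a baseline covariate and three follow-ups, so the simple calculation may well be conservative for its group effect. All of this stands.

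It can also be said that a 1-df group effect may be tested one-sided, and that the full protocol or analysis plan may say so. That stands in part. The ANCOVA's two-sidedness is inferred from the usual F-test and is not written down. But the article mentions one tail only in the power calculation, and the group-by-time test could not be one-tailed in any case.

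A reader might infer from the 70% that the study is underpowered. The documents do not support this. That figure belongs to an unadjusted comparison at 50 per group, which is neither the projected sample nor the planned test. A reader might also lower the power further for three or six comparisons, but the article plans no such adjustment. Nor does it say that a non-significant contrast, such as A versus C, will be read as evidence of no difference.

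None of this rescues the adequacy statements. Power was set for d = 0.50 on self-determination, and no sample size is enough for any effect whatever.

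**Conclusion.** The point holds as a mismatch and an overstatement, not as an arithmetic error. The 80% at 50 per group is correct for a single one-tailed two-group comparison at d = 0.50 and is not tied to the primary analysis. On that same model at two-sided 0.05, power is 70% at 50 per group and 77.5% at 60.

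The power of the planned group effect depends on correlations that the documents do not give. Under compound symmetry with correlation 0.3 to 0.6 and a constant effect, it is about 98 to 99% at d = 0.50 with 60 per group, so no claim of an underpowered trial follows.

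The two adequacy statements are wrong under either sidedness. At d = 0.30, within the plan's own medium band, unadjusted power at 60 is 50% one-tailed and 37% two-sided. Even the favourable repeated-measures assumptions bring it only to 69 to 76%. This calls for a correction of wording and does not threaten the design.

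**What to change.** In Statistical power, restate the calculation at two-sided 0.05 and label the model and its assumptions. For example:

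> With 60 youth per group and two-sided α = 0.05, power for d = 0.50 is 78% in an unadjusted comparison at a single time (minimum detectable d 0.52 at 80% power), and 88% with one baseline-adjusted follow-up at an assumed correlation of 0.5. The ANCOVA group effect averaged over three follow-ups has higher power: about 98 to 99% at d = 0.50 and 69 to 76% at d = 0.30, assuming compound symmetry with correlation 0.3 to 0.6 and a constant effect.

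Delete the clause that calls 60 per group enough for every analysis. Replace the closing sentence ("our projected sample of 60 youth will be sufficient to show any statistically significant changes in outcomes") with the minimum detectable effect for one pairwise contrast on self-determination. State the sidedness of the ANCOVA tests in Quantitative analysis, so that the two sections agree.

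The cost is wording only: no added enrolment and no change to the analysis. The downside is that the simple-model power reads slightly less favourably than before.

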#### Qualitative data: young people’s experiences of life skills programs

Fifteen randomly selected participants in Group A (RILS group) and Group C (non-residential Life Skills group) will participate in a series of semi-structured interviews before their program starts, with follow up interviews held 3 and 12 months after their program finishes. Thirty (RILS = 15, non-RILS = 15) interviews at each time point will provide adequate data (*n* = 90 total interviews) for qualitative themes to be generated and compared between time points and between groups. Theme saturation will be assessed throughout the interviewing and analysis process [40].

The interviews will last between 30 and 60 min and be conducted with the participants in their homes or by telephone, depending upon location and preference. The interviews will follow a guide developed and previously tested during pilot research with youth participants from the RILS program at the host institution [41], as well as input from knowledge users on the study team (i.e., program coordinators). The interviews will explore the following: *Pre-program*: youths’ expectations and motivations for attending; *Three months post-program:* activities and experiences they engaged in during the program, and their initial post-program experiences and reflections; *12 months post-program*: their experiences and continued reflection having had the opportunity to use the skills and learnings. Youth will be asked to reflect upon the opportunities and experiences provided during the program, and after the program finished. They will also be asked about the importance of informal peer interactions. All interviews will be digitally audio recorded and professionally transcribed verbatim.

We will also interview a parent/guardian (hereafter ‘parent’) of ten Group A (RILS program) youth participants to obtain another perspective on the program and to ascertain parent expectations and perceptions of program opportunities, experiences, and outcomes. Parents will be interviewed at the same points as the RILS youth-before the program commences, 3 months post-program, and 12 months post-program.

### Data analysis

#### Quantitative analysis

Data from the online instruments (SDS and GSE) will be downloaded into an Excel spreadsheet. Data collection for the SPS-C, MEQAS, and SEAS will use hard copies of the instruments, with data entered into the Excel spreadsheet for data management. The Excel file will then be imported into SPSS for analysis. A portion of the data will be double entered to check for accuracy. The data from the two outcome measures (SDS and GSE) will be analysed descriptively to report means and standard deviations, pre, post, and at both follow-ups (3 and 12 months). The amount of change in the outcomes will be determined across the data collection time points. Baseline (pre-program) scores of all groups will be compared using t-tests to determine whether there are significant differences between groups on the dependent variables. Attrition rates for the groups will be calculated, to determine whether differential attrition is an issue. The RILS group (Group A) will be tested against one comparison group (Groups B, C or D) in each analysis. The primary analysis will therefore be a series of two between (study groups) and three within (longitudinal measurement points) repeated measures analyses of covariance (ANCOVAs), controlling for baseline scores, with the outcome measures as the dependent variables. Effect sizes will be calculated based on difference in pre- to post-test means, using Cohen’s D, with effect sizes between 0.30 and 0.50 considered medium and those >0.60 considered large [42]. We will use multilevel modeling to assess the proportion of variance in our outcome measures associated with the three program sites.

We will describe RILS program features by calculating means and standard deviations of the MEQAS scores and examining patterns of strategy use in the SPS-C data. The SEAS data for individual youth will be collapsed within each activity setting to provide an aggregate activity profile. We will examine convergence and correspondence between the SEAS and the SPS-C and/or MEQAS. Our previous pilot work demonstrated convergence between scores on the MEQAS (observable program features) and SPS-C (observable service provider strategies) [29]. Scores on the SEAS were also further enhanced by youth-reported experiences captured during brief interviews. These initial indicators of conceptual congruence will be further explored during this study.

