### Limitations

We aim to recruit youth who are dealing with a range of complex health conditions. As in any longitudinal study, there is the potential that some participants will withdraw, due to changing desires to participate, or be lost to follow-up. However, we have put in place incentives for participants to remain involved through the full 1-year period. The youth in the RILS group are involved in the highest number of research tasks; however, the most time-intensive period of research involvement occurs during the RILS programs, which is near the beginning of the 1-year period. This may help to minimise the number of youth who decide to withdraw. Baseline data will be retained for participants who withdraw, so that comparisons may be made between them and the youth who choose to remain involved.

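### The primary repeated-measures ANCOVA, as usually run in SPSS, drops every youth who misses a follow-up; with one-third attrition planned, it discards observed scores and can bias the group contrast

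*Protocol article*

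**What the plan says.** All references are to the protocol article.

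- **Primary model (Quantitative analysis).** Group A is tested against one comparison group at a time, in "two between (study groups) and three within (longitudinal measurement points) repeated measures analyses of covariance (ANCOVAs), controlling for baseline scores". The three within-subject levels are the 1-week, 3-month and 12-month follow-ups.
- **Software (same section).** "The Excel file will then be imported into SPSS for analysis".
- **Multilevel modelling (same section).** It is named, but only to apportion outcome variance to the three program sites, not for the group comparison.
- **Attrition allowance (Statistical power).** "This will result in a total of 90 youth participants per group", and then: "We have allowed for a liberal attrition rate of one-third, which will yield a minimum enrolment of 60 youth per group".
- **Attrition checks.** Two are planned. Quantitative analysis says: "Attrition rates for the groups will be calculated, to determine whether differential attrition is an issue". Limitations adds: "Baseline data will be retained for participants who withdraw", in order to compare them with those who stay. Limitations also mentions incentives to remain in the study.

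Neither check alters the primary model. The article does not use the term complete case; the exclusion follows from the method it names.

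**The concern.** A classical repeated-measures ANCOVA holds one row per participant with all three follow-up scores. A youth who answers at 1 week and 3 months but not at 12 months is removed from all three time points. Scores already collected on the primary outcome are therefore not used, in a study that expects to lose up to a third of each group.

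The more serious consequence is possible bias. The groups are not randomised, and Limitations says that Group A carries the heaviest research load. The reasons for leaving, and how they relate to how a youth is doing after the program, could differ between Group A and its comparators. If so, completers are selected differently in the two groups, and adjustment for baseline does not remove that. The third aim, change or maintenance up to a year after the program, depends on exactly these follow-up scores.

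**Working it through.** **1. The plan's own figures.** Required n per group for d = 0.50, power 0.80, one-tailed α = 0.05:

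n = 2 × (1.645 + 0.842)² / 0.50² = 2 × 6.18 / 0.25 ≈ 49.5, so 50. This matches the article.

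After attrition: 90 × (1 − 1/3) = 60, which also matches. Power at 60 per group is 0.86 (one-tailed). Power is not the problem.

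**2. Data not used.** Per group, 60 completers supply 60 × 3 = 180 follow-up scores. The 30 non-completers could supply between 30 × 0 = 0 and 30 × 2 = 60 more, depending on when they leave. The named analysis uses none of these.

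**3. When the contrast is biased.** This was checked by large-sample simulation. None of the following assumptions comes from the article: SD 1; correlation 0.6 between any two visits including baseline; true effect 0.50 SD at each follow-up; one-third of each group leaving after the 1-week visit. Dropout follows a logistic model in the score shown, centred within group, with the slope given per SD. In the Group A only rows, low scorers leave. The estimate is the baseline-adjusted group difference among completers, averaged over the three visits.

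| Dropout depends on | Attrition, both groups | Completers, three-visit mean | Completers, 1 week |
|---|---|---|---|
| 1-week score, Group A only, slope 0.5 | 33% | 0.56 | 0.60 |
| 1-week score, Group A only, slope 1 | 33% | 0.61 | 0.68 |
| 1-week score, Group A only, slope 1.5 | 33% | 0.64 | 0.74 |
| 1-week score, opposite directions, slope 1 | 33% | 0.72 | 0.88 |
| 1-week score, same link in both groups, slope 1 | 33% | 0.50 | 0.50 |
| Baseline only, Group A only or opposite directions, slope 1 | 33% | 0.50 | 0.50 |

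A likelihood-type analysis of all observed visits gave 0.50 in every row. At 12 months the Group A only rows gave 0.54, 0.57 and 0.59. If high scorers in Group A left instead, the error would have the opposite sign.

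The range is similar at other correlations. At 0.5 and 0.7, with slopes 0.5 to 1 in one group only, the error in the three-visit mean was +0.05 to +0.12 SD. With opposite links at slope 1 it was +0.19 to +0.24 SD.

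**4. What the planned checks see.** The rates are 33% and 33% in every row, so the rate comparison shows nothing. The baseline comparison can see something: at slope 1, Group A stayers and withdrawers differ by about 0.5 SD at baseline. With 60 against 30 youth, SE = √(1/60 + 1/30) = 0.224 and 0.5 / 0.224 = 2.24, so a two-sided 5% test detects it about 60% of the time. It cannot separate the harmless case (dropout driven by baseline) from the harmful one (dropout driven by the follow-up score given baseline).

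**The case against.** The strongest case on the other side has four parts.

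- **The bias is conditional, and the mechanism is assumed.** This stands. A reader might infer that the ANCOVA is valid only if data are missing completely at random. That is too strong: the model contains baseline and group, and the last two rows of the table show no bias. If one common mechanism acts on the raw score and there is a true effect of 0.50, the completers' estimate is 0.47 to 0.48. Attrition is then 38% against 29%, which the rate check could pick up.
- **There is more than one safeguard.** This stands. Attrition rates are not the only planned check; the baseline comparison in Limitations is another. It may raise an alarm, but it leaves the primary estimate unchanged.
- **The power section does not establish a complete-case analysis set.** This stands too. Reducing 90 to 60 is ordinary conservative sizing and would be done for a mixed model as well. One might also infer that skipped surveys would push the analysed number below 50. That needs a skip rate the article does not give, added to an attrition allowance it already calls liberal.
- **Missing-data handling may sit in an analysis plan that is not shown, and imputation before the ANCOVA is compatible with the text.** This stands in part. The point here is not absent detail. The article names a primary model that, in its usual form, cannot use partial follow-up, and it reserves multilevel modelling for another question.

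**Conclusion.** The point holds in conditional form. The stated primary analysis, run in the usual way, discards observed follow-up scores from youth who miss a visit: up to 60 per group at the planned attrition. Its group contrast is biased when dropout is related to follow-up scores, given baseline, differently between groups. In the scenarios with the link in Group A only, an effect of 0.50 SD appears as about 0.56 to 0.64 over three visits while attrition rates are identical. Opposite links give 0.72.

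These sizes rest entirely on assumed mechanisms; the article supplies none, so the actual size and direction are unknown. The documents do not support saying that the analysis will be biased, or that the study is underpowered for this reason. This is a worthwhile and inexpensive improvement to a stated method, not a flaw that invalidates the study.

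**What to change.** Make the primary analysis a linear mixed model for repeated measures, for each comparison of Group A with one other group:

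- fixed effects for group, time, group × time, baseline score and baseline × time;
- unstructured covariance over the three follow-ups;
- every youth with a baseline and at least one follow-up, with all scores up to withdrawal;
- the group contrast reported at each visit.

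Keep the complete-case repeated-measures ANCOVA as a sensitivity analysis.

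The cost is a change of wording and slightly more analysis work. No new data or participants are needed; SPSS fits this model, and multilevel modelling is already planned. The limits should be stated. The mixed model relies on dropout being at random given the observed scores, and a youth who leaves before the 1-week survey still contributes no follow-up information.

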### Aims

Our specific study aims are as follows:To examine the nature of the opportunities provided by RILS programs for particular types of youth experiences, and the extent to which service providers use specific learning strategies to promote the acquisition of core skills, knowledge, and behaviours.To explore the subjective experiences of youth and parents before, during, and after the program.To assess change and/or maintenance in outcomes, namely youth development of higher-order life skills (self-efficacy and self-determination) up to 1 year post-program, when compared to three groups of matched youth.

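### The stated effect size, read literally, is an uncontrolled short-term change, so it does not express the size of the controlled one-year effect that Aim 3 asks for

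*Protocol article*

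**What the plan says.** In the protocol article, under Quantitative analysis, the rule reads "Effect sizes will be calculated based on difference in pre- to post-test means", using Cohen's d, graded "with effect sizes between 0.30 and 0.50 considered medium and those >0.60 considered large". It names no comparison group, no later time point and no standard deviation for the denominator.

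The same paragraph treats the post-program assessment and the follow-ups as different things: the outcomes will be summarised to "report means and standard deviations, pre, post, and at both follow-ups (3 and 12 months"). Table 1 places the first post-program assessment at 1 week.

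The primary analysis, by contrast, is controlled and longitudinal. "The RILS group (Group A) will be tested against one comparison group (Groups B, C or D) in each analysis", through "a series of two between (study groups) and three within (longitudinal measurement points) repeated measures analyses of covariance (ANCOVAs), controlling for baseline scores".

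The third aim is to assess outcomes "up to 1 year post-program, when compared to three groups of matched youth". The Statistical power section says that 50 per group gives "adequate power to detect moderate effect sizes (d = 0.50) on the primary outcome of self-determination".

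**The concern.** The question in Aim 3 is comparative and runs to 12 months. The effect-size rule, as worded, is neither. In youth aged 14 to 21 who are not randomised, a change from baseline combines any program effect with maturation, repeated testing and regression to the mean. The comparison groups were added to separate these. Group B is there to control for motivation and Group C to isolate the immersive component, and a pre-to-post d makes use of neither.

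At stake is how large the effect is said to be. Readers and program planners will use a standardised effect to judge that. If the published d is a pre-to-post change, it cannot be read as the benefit over any comparator. Nor can it be set against the planned d = 0.50, and it does not quantify whether gains last.

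**Working it through.** **1. What kind of d is the planned 0.50?** Inputs from Statistical power: d = 0.50, power 0.80, α = 0.05 one-tailed, 50 per group.

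- Two independent groups: n per group = 2(z₀.₉₅ + z₀.₈₀)²/d² = 2(1.645 + 0.842)²/0.25 ≈ 49.5, rounded up to 50. This reproduces the stated figure. The t-based version gives 50.15, so 51, which is close enough.
- One group, pre versus post, with 0.50 in units of the SD of change: n = (1.645 + 0.842)²/0.25 ≈ 24.7, so 25. This does not reproduce it.

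The planned d is therefore a between-group quantity. Power at 50 per group is 0.804 (normal) or 0.799 (t-based). At the 60 per group left after one-third attrition (90 × 2/3 = 60), it is 0.863 or 0.859.

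**2. What does the stated rule measure?** The documents give no means, SDs or correlations, so this step is an illustration. Assume a common baseline SD of 1. Let c be the comparator's own pre-to-post change, and assume Group A would have changed by c without its program. Let Δ be the controlled effect. Then:

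- Group A pre-to-post d = Δ + c
- between-group d = Δ

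| Δ (assumed) | c = 0 | c = 0.30 | c = 0.50 |
|---|---|---|---|
| 0 | 0 | 0.30 | 0.50 |
| 0.30 | 0.30 | 0.60 | 0.80 |
| 0.50 | 0.50 | 0.80 | 1.00 |

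The cells are Group A's pre-to-post d. With no controlled effect, the result is labelled medium once c reaches 0.30. With Δ = 0.30, it is labelled large once c exceeds 0.30. The two measures agree only at c = 0. If comparators declined (c below 0), the pre-to-post d would understate the effect. Against Group C, c also contains whatever the non-residential program achieves, so Group A's change alone cannot give the size of the immersive component.

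**3. The denominator.** Cohen's d for a change can be divided by the baseline SD or by the SD of change, and the article does not say which. With equal SDs at both times and pre-post correlation r, a change of 0.50 baseline SD becomes 0.50/√(2(1 − r)) on the second scale. This is 0.42, 0.50, 0.65 or 0.79 for assumed r = 0.3, 0.5, 0.7 or 0.8.

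**4. The labels.** Applying the stated rule, 0.30 to 0.50 is medium and 0.61 is large, while 0.51, 0.55 and 0.60 have no label. Values below 0.30 also have none, but a reader will take them as below medium.

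**The case against.** The strongest reply is that the plan already answers Aim 3. The declared primary analysis is a baseline-adjusted comparison of Group A with each comparator over three post-baseline points, and the effect size only supplements it. That stands. A reader might infer that the plan ignores its control groups or has no valid test of the RILS effect, and the documents do not support this.

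Nor does the text make this d the headline result, restrict it to Group A, or say that the whole change will be credited to RILS. If d is given for every group, a reader can set the values side by side. Means and SDs are promised at every time point, so crude standardised contrasts at 3 and 12 months could be derived.

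The sentence also follows directly on the two-group ANCOVA sentence. It could be meant as a between-group difference in pre-to-post change, in which case the objection about comparators and the mismatch with the power section would fall away. That reading is possible but not stated, and even then the rule would cover only the first post-program assessment.

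A condensed article may leave detail to an analysis plan. Here, though, the article does state a definition and cut-points, and the definition as worded does not match the aim.

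The labels carry little weight, since no test, sample size or decision depends on them. There is also no conflict with the power section on this score: 0.50 already falls in the stated medium band.

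**Conclusion.** The point holds for the reported magnitude only. As worded, the effect size is an uncontrolled short-term change. It does not express the controlled effect up to 1 year, and it is not the quantity behind the planned d = 0.50. The primary ANCOVA tests and the sample-size arithmetic are unaffected.

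It may be tempting to conclude that the published d will overstate the RILS effect. The documents do not establish that. The discrepancy equals the comparator's own standardised change, for which they give no figure. The 0 to 0.50 SD range above is assumed and includes no discrepancy at all.

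The conclusion rests on the literal reading of the sentence. The unlabelled range, above 0.50 up to and including 0.60, is a real but minor drafting gap. Severity: should fix.

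**What to change.** Replace the effect-size sentence. For each of A versus B, A versus C and A versus D, report the baseline-adjusted between-group difference from the primary model at 1 week, 3 months and 12 months. Divide it by a stated SD (the pooled baseline SD is one suitable choice) and give a 95% confidence interval. Keep within-group pre-to-post d as a descriptive summary, named as such and with its denominator stated. Make the verbal labels contiguous, or drop them.

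If a between-group difference in change was intended all along, the same sentence should say so and cover the later time points. The cost is a sentence or two of analysis text, with no new data, visits or participants.
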